### Data Collection and Sources of Data

After creating a list of eligible patients, research assistants will approach medical teams during rounds (9:00 AM to 11:00 AM) to ensure that screened patients do not have exclusion criteria (Figure 1). The assistants will then approach patients to explain the study, including basic instructions for tablet use (on/off, opening/closing applications, and typing with touchscreen); intervention patients only will receive additional instruction in the form of the semistructured tutorial. The assistant will then leave the device with the patient and return to recollect it after about 4 to 5 hours. The assistant will perform a debrief interveiw upon return and ask patients to view and verify their preadmission medications using the medication list in their PHR. Success (gross pass/fail) in this task will be defined as patient ability to independently log in, locate their medication list, and verify their prehospitalization prescriptions (MyChart does not show inpatient medications unless they are continued at discharge). We will not require patients to correctly describe indications for every medication to receive credit; they will only be asked to identify which medications are familiar to them and which are not. We will use frequency analysis to compare the percentage of intervention group who are able to complete this task with the control group.

Sources of data will include surveys that will be administered on the device, semistructured debrief interviews administered by assistants, and data on postdischarge access to the PHR from our EMR data repositories. All patients will answer basic questions about demographics, health literacy, and technology use in a preuse survey. The postuse survey will ask about satisfaction with the device to access their PHR and any technical issues. We have developed an interview tool for assistants to use to collect information about patient-reported problems with devices and ask open-ended questions about the overall experience using the tablet. During the debrief interview, the assistant will also ask the patient to demonstrate ability to access their PHR to view and verify their preadmission medications using their PHR medication list. Data about patient use of their PHR is compiled by our EMR in a searchable database (Clarity). We will query Clarity at 7 days to determine access and specific PHR tasks accomplished by all patients both during their hospital stay and for 7 days after discharge. We will also use the Clarity database to identify our virtual cohort of patients who were already engaged with their PHR (1 or more log-ins in the month prior to hospitalization) and were hospitalized during the same 12-month period of our study.

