#### Aim 2: To Compare Effects of an Inpatient PHR Engagement Intervention to a Virtual Cohort.

We will compare PHR engagement of our study participants to a virtual cohort of patients who were hospitalized but who were already regular users of their PHR. Patients in this virtual cohort will be identified through review of EMR data only and receive no intervention—they will serve as a benchmark for all participants (both intervention and control) in our study.

We hypothesize that those in the intervention group will be more likely than the control group to use their PHR while they are inpatients and after discharge and that patients in both the intervention and control groups will be more likely to use their PHR in these settings than the virtual cohort. In addition to testing these hypotheses, our project is designed to have significant impact on patient engagement with their care during hospitalization at our hospital. We will also add significant value to existing efforts by our health system to increase patient use of existing technologies: our system uses the PHR application called MyChart (Epic Systems Corp), a Web-based patient portal that allows patients to access to their PHR and perform health care tasks such as sending messages to providers, requesting appointments, viewing test results, and reviewing their medications. The overall objective of this research is to study the use of mobile platforms to improve transitions in care for older, hospitalized adults.

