### Data Analysis

Our overall objective is to assess whether inpatients can successfully use iPads for clinically useful tasks such as viewing their medications or labs or messaging their providers by using their PHR. First, we will assess this overall goal using descriptive statistics (frequency analysis) to describe time required to orient patients to tablets and basic use metrics for PHR (time spent using PHR, number of PHR tasks observed by assistant, etc). Next, we will determine the total number of log-ins to the PHR and number of clicks on different domains of the PHR (medications, labs, appointments) by querying the PHR database. We will extract basic information about whether each patient has accessed their PHR (successful log-in), when they first logged in (time from discharge), and how many times they logged in. Additionally, we will extract information about specific tasks accomplished at any point during both inpatient and postdischarge periods. We will use frequency analysis to compare the following for intervention versus control patients: rates of PHR access, time to first log-in, total number of log-ins, and number of specific tasks (refill prescription, make/change appointment, view test result, or send message to provider) accomplished within 7 days. Finally, we will assess patient satisfaction with devices overall and PHR use specifically. We will perform bivariate analyses (chi-square tests) to determine whether ability to perform key PHR tasks (eg, view medications or lab results) vary according to demographics such as age, gender, health literacy, or technology usage (eg, types of devices owned, frequency of Internet use). Although most of our findings will be descriptive, we plan to enroll 100 patients to enable detection of a 10% difference in ability to perform a key inpatient task (medication verification) and one of several key postdischarge PHR tasks (80% power, 2-sided alpha 0.05).

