Among older adults, 70% (15) owned a laptop, 58% (13) owned a desktop computer, 52% (11) owned a smartphone, and 42% (9) owned a tablet. Thus, mobile technologies pose an excellent venue to interact with this patient population. Trained research assistants spent at least 30 minutes with those patients who needed more assistance to become familiar with the tablets, but the majority needed 15 minutes or less, suggesting that most of them felt comfortable with using this technology. Indeed, our findings to date suggest that inpatients of all ages in both intervention and control groups require only minimal orientation from research assistants to use basic (eg, access Internet, check email) as well as more advanced functions (watch videos, complete tasks requiring more advanced navigation): 90% (41) of patients required 30 minutes or less for device orientation and 81% (36) required 15 minutes or less. Additionally, we found that after focused bedside teaching, most patients in our study were able to perform one or more key function in their PHR. These key functions included viewing their medication list (34, 76%), viewing scheduled appointments (38, 85%), viewing test results (38, 85%), and sending a secure message to their primary care provider (37, 82%). Additionally, 75% (34) reported they were satisfied or very satisfied with iPad tablet use for bedside access to their PHR to accomplish these tasks.

Because data is still being collected to compare patient groups within our study (intervention vs control), we compared PHR use among all participants (to date) in both groups to a virtual cohort of patients identified as regular users of their PHR prior to hospitalization. In most areas, both groups were similar, but our study group had significantly higher activity in medication list views (mean 2.12 views vs 1.07) and the virtual cohort had significantly higher use of the provider messaging function (mean 4.34 views vs 1.63) (Table 2).

**Table 2 table2:** Patient characteristics and PHR use in study participants compared to a virtual cohort of regular PHR users.

		Study group (n=45)	Virtual cohort (n=400)	*P* value
Inpatient characteristics				
	Hospital length of stay, days	5.79	4.51	.37
	Previous PHR experience, n (%)	22 (50)	400 (100)	<.01
PHR use during hospitalization				
	Logins per person, mean	2.74	2.99	.64
	Medication tab views, mean	2.12	1.07	<.01
	Test results tab views, mean	1.42	2.21	.28
	Appointments tab views, mean	0.69	1.34	.11

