	Provider messaging inbox views, mean	1.63	4.34	.04
PHR use after hospitalization (up to 7 days after discharge)				
	Logins per person, mean	4.04	3.87	.83
	Medication tab views, mean	2.93	1.46	<.01
	Test results tab views, mean	6.28	4.29	.37
	Appointments tab views, mean	2.72	2.01	.32
	Provider messaging inbox views, mean	3.91	6.11	.36

**Table 3 table3:** Adjusted PHR use during hospitalization by study group compared to virtual cohort group.

	Multivariable logistic regression^a^	
	OR for study group vs virtual cohort group mean	95% CI
Medication tab views	2.4	1.5-4.2
Test results tab views	1.1	0.7^-^1.8
Appointments tab views	0.71	0.5^-^1.1
Provider messaging inbox views	0.70	0.5^-^1.1

^a^Adjusted for age, gender, race/ethnicity, length of stay, and prior PHR experience.

In analyses adjusted for confounding, the higher rate of provider messaging seen in Table 3 disappeared with adjustment; however, the higher rate of medication list views persisted (odds ratio [OR] 2.4) (Table 3). In adjusted analyses of PHR use after discharge, there were no significant differences between the virtual cohort and the study group.

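### As written, the in-hospital PHR counts set against the virtual cohort do not leave out the log-in and medication-list view that staff request of every participant at debrief

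*Protocol article*

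**What the plan says.** Under Data Collection and Sources of Data, the assistant leaves the tablet with the patient, returns after about 4 to 5 hours, holds a debrief interview, and at that point will "ask patients to view and verify their preadmission medications using the medication list in their PHR". Passing requires an independent log-in as well as finding the list. The same section repeats the request: "During the debrief interview, the assistant will also ask the patient to demonstrate ability to access their PHR to view and verify". It applies to both arms.

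The counts come from the EMR database: "We will query Clarity at 7 days to determine access and specific PHR tasks accomplished by all patients both during their hospital stay". The window also covers the first week at home. Data Analysis adds total log-ins and clicks by domain (medications, labs, appointments), and then: "Additionally, we will extract information about specific tasks accomplished at any point during both inpatient and postdischarge periods".

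Aim 2 identifies the virtual cohort from EMR data only, with no intervention, yet hypothesizes that "patients in both the intervention and control groups will be more likely to use their PHR in these settings than the virtual cohort", the settings being inpatient and post-discharge. Principal Findings confirms that the cohort had neither tablets nor PHR help.

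Results already reports this comparison for 45 participants against 400 cohort patients (Table 2). Table 3 is titled "Adjusted PHR use during hospitalization by study group compared to virtual cohort group" and gives an odds ratio of 2.4 (95% CI 1.5 to 4.2) for medication views. For the later period, "In adjusted analyses of PHR use after discharge, there were no significant differences between the virtual cohort and the study group".

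**The concern.** The debrief request is a test. It sits under data collection, not under Randomization and Intervention, and its result is scored separately as pass/fail. A patient who complies produces a log-in and a medication-list view during the hospital stay, which is the window the query covers. No step sets that session aside, so the test is credited as engagement in the study group. The cohort has no matching event.

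At stake is the in-hospital half of Aim 2 for medication views and for log-ins or any access. Medication views matter most. They are the one tab the debrief asks everyone to open, and the only in-hospital measure in Table 2 on which the study group exceeds the cohort. Principal Findings already says that participants were more likely to view medications in hospital, and suggests that tablets with basic help may improve engagement. Limitations does not mention the requested views.

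**Working it through.** **Inputs**
- In-hospital medication views per person (Table 2): study group 2.12, cohort 1.07, P<.01.
- In-hospital log-ins per person (Table 2): 2.74 vs 2.99, P=.64.
- Post-discharge medication views, unadjusted (Table 2): 2.93 vs 1.46, P<.01.
- Participants who reached the medication list page (Table 1): 34 of 45.
- Appointments (Tables 1 and 2): 38 of 45 reached the page independently; 0.69 in-hospital views per person.

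The Table 2 means come from patient-level data that are not shown, so they are taken as given.

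**Step 1: the observed excess.** In hospital: 2.12 − 1.07 = 1.05 views; ratio 2.12/1.07 = 1.98. After discharge, with no debrief: 2.93 − 1.46 = 1.47; ratio 2.93/1.46 = 2.01.

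**Step 2: what one requested view could contribute.** Let s be the share of participants who opened the list when asked and c the share of those views that Clarity recorded, each view being additional to the patient's own use. Remaining excess = 1.05 − s × c. The protocol gives no value for c, and taking s between 34/45 and 1 is an assumption.

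| s | c | Contribution | Remaining excess | Share of excess |
|---|---|---|---|---|
| 45/45 | 1 | 1.00 | 0.05 | 1.00/1.05 = 95% |
| 34/45 = 0.76 | 1 | 0.76 | 0.29 | 0.76/1.05 = 72% |
| any | 0 | 0 | 1.05 | 0% |

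The requested view could therefore explain anything from none to about 95% of the excess.

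**Step 3: a check on capture.** 0.69 × 45 = 31 in-hospital appointment views in total, yet 38 patients were seen to reach that page. At least 7 observed visits are missing from the counts. This shows that observed page visits are not always in the Table 2 figures. It does not say why, and it gives no capture rate for medication views.

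**Step 4: log-ins.** The study group is already lower: 2.74 − 2.99 = −0.25. One recorded debrief log-in per person is the upper bound of the correction: 2.74 − 1 = 1.74, a difference of −1.25. The number actually recorded is not given.

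**Step 5: the randomized arms.** Both arms get the same request. An equal addition k cancels in a difference of means: (a + k) − (b + k) = a − b. A yes/no measure of any in-hospital access would be pushed up in both arms, by an amount the article does not allow to be sized.

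The odds ratio of 2.4 in Table 3 cannot be reworked from means; it needs the patient-level counts.

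**The case against.** The strongest reply is that inclusion is inferred. No sentence says that debrief clicks are counted, the appendices and the workflow figure are not shown, and query filters are often left to a fuller document. Data Analysis also lists tasks observed by the assistant separately from database counts. What stands is that inclusion is an inference and should be worded as one. But the article goes beyond silence: it fixes a rule covering the whole stay, and that rule, followed as written, takes in the test.

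Second, the data do not show that the prompt drives the excess. The unprompted, unadjusted ratio after discharge (2.01) is about the same as in hospital (1.98), and the appointment counts fit exclusion or non-recording of staff sessions as well as partial capture. This stands. The non-significant adjusted post-discharge result weakens the first part without removing it. A reader might take 31/38 as a capture ceiling for medication views, but nothing in the article supports carrying that figure from one tab to another.

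Third, a reader might infer that the whole in-hospital comparison favors the study group. The article does not support that. The debrief asks for no test-result, appointment or messaging views, and prior PHR experience (50% vs 100% in Table 2) pushes the unadjusted contrast the other way.

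Fourth, the comparison is a non-randomized benchmark in a mostly descriptive study, and Conclusions calls use similar to the cohort's. This limits the weight of the point. Aim 2 still states a directional hypothesis, and a conclusion on medication views has been drawn.

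**Conclusion.** The point holds within limits. Followed as written, the query credits a study-requested log-in and medication-list view to the study group and has nothing equivalent in the cohort. The in-hospital Aim 2 comparison of medication views, and of log-ins or any access, is inflated for the study group by up to about one event per person.

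The true amount is unknown. At full capture, with each requested view additional to own use, it is 0.76 to 1.00 of the 1.05-view excess; at no capture it is zero. It would be tempting to call the medication-view finding an artifact. The documents do not support that: capture is not given, and the post-discharge doubling suggests that part of the excess may be real.

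A reader might also extend the point to the randomized comparison. The difference in means between arms is not affected, assuming the request is carried out and recorded about equally in both. The pass/fail task and the post-discharge outcomes are also untouched. Tablets, log-in help and the tutorial are declared parts of the package and are not criticized here.

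**What to change.** Record the start and end time of the debrief on the existing form. Exclude Clarity log-ins and medication clicks in that window from the in-hospital comparison with the cohort, either as the main analysis or reported with and without. Keep set-up and tutorial use in the counts as part of the package, reported separately if wished.

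For participants already enrolled without session times (45 of the planned 100 at the time of writing), add a sensitivity analysis that removes one log-in and one medication view per person, at least for those who completed the task. State that it may overcorrect where the requested view was not recorded or replaced one of the patient's own. Rerun the adjusted medication-view model on the same basis, and qualify the in-hospital medication-view statement in Principal Findings.

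The cost is two clock times per patient and a time filter in the query. Time to first log-in is already extracted and tasks are already split at discharge, so some timing is held. The article does not say whether individual clicks carry a clock time; if they do not, the sensitivity analysis has to serve for everyone. The in-hospital counts become slightly smaller and less precise. No extra patients are needed.

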**Figure 1 figure1:**
[figure not shown]
Inpatient iPad tablet daily workflow.

### Data Analysis

Our overall objective is to assess whether inpatients can successfully use iPads for clinically useful tasks such as viewing their medications or labs or messaging their providers by using their PHR. First, we will assess this overall goal using descriptive statistics (frequency analysis) to describe time required to orient patients to tablets and basic use metrics for PHR (time spent using PHR, number of PHR tasks observed by assistant, etc). Next, we will determine the total number of log-ins to the PHR and number of clicks on different domains of the PHR (medications, labs, appointments) by querying the PHR database. We will extract basic information about whether each patient has accessed their PHR (successful log-in), when they first logged in (time from discharge), and how many times they logged in. Additionally, we will extract information about specific tasks accomplished at any point during both inpatient and postdischarge periods. We will use frequency analysis to compare the following for intervention versus control patients: rates of PHR access, time to first log-in, total number of log-ins, and number of specific tasks (refill prescription, make/change appointment, view test result, or send message to provider) accomplished within 7 days. Finally, we will assess patient satisfaction with devices overall and PHR use specifically. We will perform bivariate analyses (chi-square tests) to determine whether ability to perform key PHR tasks (eg, view medications or lab results) vary according to demographics such as age, gender, health literacy, or technology usage (eg, types of devices owned, frequency of Internet use). Although most of our findings will be descriptive, we plan to enroll 100 patients to enable detection of a 10% difference in ability to perform a key inpatient task (medication verification) and one of several key postdischarge PHR tasks (80% power, 2-sided alpha 0.05).

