#### Aim 1: To Promote Inpatient Engagement With Their PHR During and After Hospitalization.

We will analyze patients’ use of their PHR throughout hospitalization and also for 7 days after discharge to determine if our intervention affects likelihood of PHR use to view medications, check lab results, view appointments, or send a provider message.

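### Domain-level PHR use is a raw count of clicks or tab views, which cannot show whether more patients used a function or used it on more occasions

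*Protocol article*

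**What the plan says.** All references are to the protocol article.

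- **Aim 1** is about probability of use. The data will serve "to determine if our intervention affects likelihood of PHR use to view medications, check lab results, view appointments, or send a provider message". The hypotheses under Aim 2 have the same form: intervention patients likelier to use the PHR than controls, and both arms likelier than the virtual cohort.
- **Data Analysis** extracts volume: "Next, we will determine the total number of log-ins to the PHR and number of clicks on different domains of the PHR". The domains named are medications, labs and appointments.
- **Data Analysis, arm comparison**, lists "rates of PHR access, time to first log-in, total number of log-ins, and number of specific tasks", the tasks being "refill prescription, make/change appointment, view test result, or send message to provider) accomplished within 7 days". Clicks are not on this list. Nor is viewing medications or viewing appointments, although Aim 1 names both.
- **Data Collection and Sources of Data** has every participant open and verify the medication list at the debrief. This is scored by observation: "Success (gross pass/fail) in this task will be defined as patient ability to independently log in, locate their medication list". Only the intervention arm receives the tutorial. The virtual cohort receives neither.
- **Results** reads the counts as activity: "our study group had significantly higher activity in medication list views (mean 2.12 views vs 1.07" in the cohort. It then reports higher messaging use in the cohort from 4.34 against 1.63 inbox views. The Discussion goes on to say that participants were likelier to view their medications, and it plans to benchmark each arm separately against the cohort.

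**The concern.** A mean number of tab views does not answer a question about likelihood of use. It rises when more patients open a page, when the same patients open it on more occasions, when a page is reopened within one visit, and when a research assistant asks for it to be opened. Only the first two are what the aims ask about. Table 2 gives the means alone, so a reader cannot tell these sources apart.

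At stake is mainly the Aim 2 benchmark, where the two significant inpatient contrasts are both tab-view means and are described as differences in use. Aim 1 is touched more narrowly. For viewing medications and viewing appointments, domain clicks are the only database measure that Data Analysis names, and the task "view test result" in effect comes close to a page view.

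**Working it through.** **Inputs (Table 2, means per person, study group vs virtual cohort)**

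| | Inpatient | After discharge |
|---|---|---|
| Log-ins | 2.74 vs 2.99 (P=.64) | 4.04 vs 3.87 (P=.83) |
| Medication views | 2.12 vs 1.07 (P<.01) | 2.93 vs 1.46 (P<.01) |
| Test result views | 1.42 vs 2.21 | 6.28 vs 4.29 |
| Appointment views | 0.69 vs 1.34 | 2.72 vs 2.01 |
| Inbox views | 1.63 vs 4.34 (P=.04) | 3.91 vs 6.11 (P=.36) |

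The P values cannot be reproduced, because no standard deviations or test are given.

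**Step 1. Repeat views exist.** If each view belongs to a counted log-in, a log-in can supply at most one first view of a tab. Repeats per patient are then at least views minus log-ins.

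- Cohort inbox, inpatient: 4.34 − 2.99 = 1.35, and 1.35/4.34 = 31% of views.
- Cohort inbox, after discharge: 6.11 − 3.87 = 2.24, and 2.24/6.11 = 37%.
- Study group test results, after discharge: 6.28 − 4.04 = 2.24, and 2.24/6.28 = 36%.

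**Step 2. Where the inpatient differences sit.** Mean views = mean log-ins × (mean views / mean log-ins). The log-in ratio is 2.74/2.99 = 0.92.

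- Medication: 2.12/2.74 = 0.77 vs 1.07/2.99 = 0.36, ratio 2.16. Share on the log scale: ln(2.162)/ln(1.981) = 113%, since log-ins run the other way.
- Inbox: 1.63/2.74 = 0.59 vs 4.34/2.99 = 1.45, ratio 0.41. Share: ln(0.410)/ln(0.376) = 91%.

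These are ratios of group means, without standard errors. With log-ins nearly equal, any tab difference must appear here, so the shares locate the difference without explaining it.

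**Step 3. The same means fit opposite readings.**

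- Medication, no repeats: a single view in 77% vs 36% of log-ins gives the observed means exactly, which would be more occasions of use.
- Medication, equal occasions: 1.07 sessions with a view in each group also fits, with 2.12/1.07 = 1.98 views per such session in the study group and 1.00 in the cohort.
- Inbox, equal occasions: 1.63 sessions with a view in each group fits, with 1.00 vs 4.34/1.63 = 2.66 views per such session.

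The proportion of patients with at least one view cannot be computed from the article.

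**Step 4. Prompted views.** The number logged at the debrief is not given. Assuming 0.5 to 1.0 per participant, the unprompted inpatient medication mean is 2.12 − 0.5 = 1.62 to 2.12 − 1.0 = 1.12, against 1.07 in the cohort. The ratio falls from 1.98 to between 1.51 and 1.05.

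**Step 5. Is prompting the whole story?** Not shown. After discharge, where no debrief applies, medication views are still 2.93 vs 1.46 (0.73 vs 0.38 per log-in), although the Results report no significant post-discharge differences after adjustment.

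**The case against.** The strongest reply is that clicks are not how the trial judges its randomised comparison. That list holds access, time to first log-in, log-ins and tasks. The key inpatient task is an observed pass/fail, and the plan calls most of its findings descriptive. This stands, and it confines the Aim 1 part to viewing medications and appointments.

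Second, Table 3 gives an adjusted odds ratio of 2.4 (1.5 to 4.2) for medication views, and logistic regression ordinarily takes a yes/no outcome. If that outcome is any view against none, repeat clicks cannot have produced it. But the article does not define the outcome, and an any-view outcome would still include the debrief view.

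Third, event coding is often left to a fuller document. That is fair for session rules. It does not cover the choice of tab-view means, which the article states and already reports.

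A reader might go further and infer that untrained patients hunt for pages, so that controls look more engaged than trained patients. The documents do not support this:

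- Table 2 pools both arms, and no arm-level data are reported.
- Its two significant inpatient differences run in opposite directions.
- Medication views are below one per log-in in both groups, so they require no repeat clicking.
- Over the four inpatient tabs, the experienced cohort has more views per log-in (8.96/2.99 = 3.00) than participants (5.86/2.74 = 2.14), which runs against poor navigation as the driver.
- Tutorial views, if logged, would push the other way by inflating the intervention arm.

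**Conclusion.** The point holds as a mismatch between the aims and the domain-level measure. The aims ask about likelihood of use, while Data Analysis and Table 2 count views. At least 31% of the cohort's inpatient inbox views were repeats within a log-in, provided every view falls in a counted log-in. Prompted medication views could account for anything from a modest part to nearly all of the inpatient medication gap, under the assumed 0.5 to 1.0 views per participant. So neither 2.12 vs 1.07 nor 1.63 vs 4.34 can be read as more patients or more occasions of use.

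For Aim 1 the same limit applies to viewing medications and viewing appointments. The size and direction of any bias between arms are unknown. Access, time to first log-in, log-ins, completed tasks and the observed pass/fail are not tab-view counts and do not share the problem in this form, apart from the test-result task noted above. The change is worth making now: 45 of 100 patients are enrolled and the arms have not been compared.

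**What to change.** For each patient and domain, derive two measures from the same Clarity records:

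1. any view, yes/no;
2. the number of distinct log-in sessions, or days, with at least one view.

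Exclude views made during the tutorial and the debrief, or report the post-discharge period separately. Without this step the any-view measure for medications would be driven by the debrief request in both arms, and in the intervention arm also by any tutorial views that are logged. Use these measures for the cohort benchmark and for any domain-level comparison of the arms. Keep raw clicks as description, and state the outcome behind the Table 3 odds ratios.

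The cost is re-coding of data already queried, plus a record of when each tutorial and debrief took place. Session time stamps must be available. They probably are, since the plan extracts time of first log-in and splits use at discharge. The downside is that genuine repeat views within one session no longer add to the outcome.
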